**Figure 2 F2:**
[figure not shown]
**(**A) Pressure Pain Detection Threshold, Temporal Summation of Pain and Conditioned Pain Modulation test location, 5 cm from the lateral epicondyle on the brachioradialis muscle. (B) Heat Pain Threshold and Offset Analgesia probe location on the volar forearm, 4 cm distal to the elbow joint and 4 cm proximal to the wrist using the centre line from the elbow to the wrist, a cross is marked out 6 cm deep and 4 cm wide.

Handheld pressure algometer (Algomed, Medoc, Israel (laboratory), Force Ten FDX, Wagner Instruments, USA (Clinical)) with a 1 cm^2^ tip will be used to apply pressure at a gradual rate of 50 kPa/s^53^ to assess PPT. The participant will press a handheld button (laboratory) or say ‘Stop’ (Clinical) when the sensation of pressure changes to pain or discomfort. PPT will be calculated as the mean of three replicates separated by at least 1 min or until any lingering feelings have subsided. Lower values indicate greater sensitivity.

A 256 mN punctate stimulator (Laboratory—MRC Systems, Germany) or monofilament (Clinical—OptiHair2, MRC Systems, Germany) will assess TSP. A single stimulus will be applied, followed by a train of 10 repeated stimuli at a rate of 1/s^54^ based on prior training. The participant will be asked to rate their pain intensity from 0 ‘no pain or sharpness’ to 10 ‘worse pain or sharpness’ on a Visual Analogue Scale (VAS) after the single and the average of 10 repeated stimuli. TSP will be calculated as the VAS of 10 stimuli minus the VAS of a single stimulus.^51^ An average of 10 will be used to include the most painful stimuli, as they don’t always occur as the 10th stimulus.^55^ The mean of two replicates separated by 5 min will be calculated.^51^ Large positive values for TSP indicate greater sensitivity (likely more efficient spinal integration).

Using the Advanced Pain Discovery Platform CPM protocol, PPT will be measured before and after a pain-conditioning stimulus. The unconditioned stimulus will be the average of three trials on the non-dominant brachioradialis muscle. A 15 cm wide pressure cuff on the dominant forearm will be inflated to occlude arterial blood flow. Participants will be asked to squeeze a stress ball until they indicate pain levels of 4/10 (0=no pain, 10=worst pain imaginable) due to ischaemic pain,^56^ at which point PPT is performed again before the cuff is released. The CPM effect will be calculated as the mean of three unconditioned PPT minus the conditioned PPT.^56^ Thus, negative values indicate an inhibitory CPM effect and positive values a facilitatory effect.^56^ To account for measurement error, the within-participant coefficient of variation (CoV) of the unconditioned PPT will be determined; only the CPM effect greater in magnitude than the CoV will be considered a true response.^57^

HPT will be assessed using a 6.6×4×4.4 cm probe (TCS II, QST.Labs, France) applied to the non-dominant volar forearm. To overcome adaptation or sensitisation, the forearm is divided into four zones (figure 2), with the probe moved from zone to zone between stimuli.^58^ The method of limits will be used to establish the heat thresholds. A computer-controlled heat stimulus will be applied, with the baseline temperature set at 32°C and increasing at a rate of 1°C/s to a maximum of 50°C.^57^ The participant will indicate using a handheld button when the sensation of heat changes to one of pain, at which point the test is stopped. HPT is calculated as the mean of three replicates taken 10 s apart. Lower HPT values indicate greater sensitivity to thermal pain.

Offset analgesia will be measured using a tonic heat stimulus train to the skin of the non-dominant volar forearm (figure 2). The study temperature will be individualised. Starting at baseline (32°C), the first temperature will be set to HPT for 10 s, then returned to baseline and increased by 1°C. The participant will continuously rate their pain on an electronic VAS (eVAS). When the eVAS reaches 50/100, the test will be stopped^58^ and the actual temperature recorded. Pain^50^ will be determined as the average of two trials separated by 1 min. To ensure the tonic heat stimulus is noxious for the offset analgesia protocol, the following rule will apply:

Pain^50^<45°C then tonic heat stimulus=Pain^50^+2°C.

Pain^50^≥45 °C then tonic heat stimulus=Pain.^50^

The offset analgesia paradigm will consist of three continuous phases: (T1) initial tonic heat stimulus (5 s); (T2) tonic heat stimulus+1 °C (5 s); (T3) tonic heat stimulus (20 s).^16^ After T3, the temperature will decrease back to baseline (75°C/s). The control paradigm will consist of a constant tonic heat stimulus for 30 s. Participants will continuously rate their pain from 0 as ‘no pain’ to 100 as ‘worst pain imaginable’ on the eVAS.^10^ Two offset analgesia and two control trials will be undertaken in random order, randomised to the volar forearm zone. Offset analgesia will be determined based on the following approaches: Peak eVAS (T2); min eVAS (T3); ΔeVAS=peak eVAS−min eVAS; ΔeVAS corrected = (ΔeVAS/peak eVAS)×100.^59^ The following approaches will also be explored: difference in average pain rating T3 (16 s–20 s) between control and offset analgesia,^60^ difference in average pain rating T1 (4 s–5 s) and T3 (16 s–20 s). If the alternative approaches are more reliable in this population, the most reliable will be taken forward. Positive scores indicate the presence of offset analgesia.

In addition to the clinical QST, tenderness to nail blanch pressure of the assessor (approx. 4 kg) will be assessed at 18 sites (bilateral occiput, trapezius, supraspinatus, low cervical, second rib, lateral epicondyle, gluteal, greater trochanter, knee). Each site is classified as ‘tender’ or ‘not tender’, according to whether the participant felt the stimulus as only pressure, or as pain.^61^ The total number of tender sites will be used to index pressure pain sensitivity.

Immediate and delayed word recall (memory), animal naming (semantic fluency) and letter cancellation (visuospatial) will assess cognitive function.^62 63^ Neuropathy will be evaluated as a potential confounder through sensory and reflex neurological assessment, including knee and ankle reflexes, along with four sensory tests (touch pressure, pinprick, vibration, joint position) on the dorsal surface of the great toe using the modified Neuropathy Impairment Score in the Lower Limb.^64^

Sleep quality will be assessed using the self-reported Pittsburgh Sleep Quality Index^65^ and indirectly through wrist-worn actigraphy (wGT3X-BT, Actigraph, USA) on seven consecutive nights following the baseline study visit. Sleep diaries will validate actigraphy data, before calculating sleep onset latency, total sleep time, number of awakenings, total wake time and sleep efficiency.^66^

All participants will complete the Widespread Pain Index and the Symptom Severity Scale (SSS) to classify fibromyalgia according to the American College of Rheumatology (ACR) fibromyalgia criteria.^67^ Possible or probable nociplastic pain will be classified using the IASP Nociplastic Pain clinical criteria.^68^ Hand, hip, and knee osteoarthritis will be classified using the EULAR-ACR clinical criteria.^69^,^72^ For individuals reporting inflammatory arthritis, participants will be assessed against condition-specific criteria: ACR/EULAR rheumatoid arthritis (RA)^73^; the Modified New York criteria for axial spondyloarthritis^74^; the Classification Criteria for Psoriatic Arthritis^75^ for PsA. Individuals with RA and PsA will be assessed using the 28-joint Disease Activity Score.^76^

All participants will have a baseline blood sample taken. High-sensitivity C reactive protein will be evaluated as an inflammatory marker.

Questionnaires completed at baseline, 6, and 12 weeks will assess clinical characteristics associated with maladaptive pain processing, patient-centred outcomes and potential confounders. Characteristics related to augmented central pain processing will be evaluated using the Cognitive Failures Questionnaire,^77^ Hospital Anxiety and Depression Scale,^78^ Bristol Rheumatoid Arthritis Fatigue Scale,^79^ Pain Catastrophising Scale,^80^ Self-Reported Leeds Assessment of Neuropathic Signs and Symptoms^81^ and the Pittsburgh Sleep Quality Index.^65^ The CSI Short-Form (CSI-9)^40^,^43^ will be used as an alternative for comparison with CAP.

Patient-centred outcomes will assess pain severity (Numerical Rating Scale^82^), quality (McGill^83^) and periodicity (pain diaries^84 85^), disability (Health Assessment Questionnaire^86^) and global quality of life (36-item Short Form Survey^87^). Potential confounders will also be included in the questionnaire, including demographics (age, sex, ethnicity, social deprivation,^88^ amenorrhea status), comorbidities (Rheumatic Disease Comorbidity Index^89^). Regular and current medication used will be classified as analgesic (subclassified: paracetamol, Non-steroidal anti-inflammatory drugs, anti-neuropathic (antidepressant, anti-convulsive), strong/weak opioid, other).

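### The rule for a true CPM response compares a pressure difference with a unitless CoV, and even on one scale a one-CoV threshold does not account for measurement error

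*Protocol article*

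**What the plan says.** The rule is in the protocol article, Methods and analysis, Experimental procedures, in the paragraph on the CPM protocol.

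- **CPM effect:** "The CPM effect will be calculated as the mean of three unconditioned PPT minus the conditioned PPT". No division by baseline is mentioned. The PPT paragraph says the algometer "will be used to apply pressure at a gradual rate of 50 kPa/s", so PPT and any difference between PPTs are pressures.
- **Readings:** "The unconditioned stimulus will be the average of three trials on the non-dominant brachioradialis muscle". After conditioning, the text says only that participants squeeze a ball until pain reaches the target, "at which point PPT is performed again before the cuff is released".
- **Direction:** "negative values indicate an inhibitory CPM effect and positive values a facilitatory effect".
- **Threshold:** the stated purpose is "To account for measurement error". For this, "the within-participant coefficient of variation (CoV) of the unconditioned PPT will be determined", and "only the CPM effect greater in magnitude than the CoV will be considered a true response". No multiplier and no conversion between scales is given.

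**The concern.** There are two separate problems.

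1. **Units.** A CoV is an SD divided by a mean, so it is a ratio or a percentage. The CPM effect as defined is a pressure. One cannot exceed the other in any meaningful sense until a common scale is named.
2. **Threshold.** The CoV describes the scatter of single unconditioned readings. The quantity being judged is a difference, which also carries the error of the conditioned measurement. A cut-off of one CoV makes no allowance for that, for the poor precision of an SD from three readings, or for any chosen error rate.

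CPM is one of the three clinical QST modalities in the proposed tool and is also measured with the laboratory device (Abstract; Table 1). A response label that is often assigned to people with no effect would be a weak descriptor, and would carry noise into any analysis that used it.

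**Working it through.** The article states no misclassification rate, so there is no figure to reproduce. The check asks how often a person with no CPM effect passes the rule.

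**Inputs from the article:** three unconditioned readings; a threshold of 1 × CoV applied to the magnitude, so in both directions; one conditioned reading on the plain wording, with no number stated.

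**Assumptions:** no true CPM effect; independent normal readings with the same within-person SD, σ, before and during conditioning.

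**Step 1: a common scale.** CoV × unconditioned mean = SD. So comparing CPM as a percentage of the unconditioned mean with the person's CoV% is the same as comparing the kPa difference with the person's SD in kPa. All results below use this common scale.

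**Step 2: error SD of the difference.** With m conditioned readings, SD(D) = σ × √(1/3 + 1/m).
- m = 1: σ × √(4/3) = 1.155σ
- m = 3: σ × √(2/3) = 0.816σ

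**Step 3: the threshold in error SDs.**
- m = 1: 1/1.155 = 0.866
- m = 3: 1/0.816 = 1.225

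**Step 4: chance of passing with no effect.** With the person's own SD (n−1 divisor, 2 df) the reference is t on 2 df, for which P(|t| > x) = 1 − x/√(2 + x²). With a pooled, well-estimated CoV it is the normal distribution.

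| Conditioned readings | Own CoV | Pooled CoV |
|---|---|---|
| 1 | 1 − 0.866/√2.75 = 47.8% | P(\|Z\| > 0.866) = 38.6% |
| 3 | 1 − 1.225/√3.5 = 34.5% | P(\|Z\| > 1.225) = 22.1% |

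Both directions are counted. By symmetry, false inhibitory responders are half: about 24% and 19% with one conditioned reading, about 17% and 11% with three.

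**Step 5: simulation** (10⁶ draws per setting, one conditioned reading, own CoV; assumed PPT means of 150, 250 and 400 kPa and assumed CoVs of 5–30%). The rate was 47.7–47.9% throughout, so on a common scale it does not depend on PPT level or on the size of the CoV. Lognormal readings with 10–30% variation gave 47.2–47.7%.

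**Step 6: threshold for a 5% two-sided null rate.**
- Pooled CoV: 1.96 × 1.155 = 2.26 CoV (m = 1); 1.96 × 0.816 = 1.60 CoV (m = 3).
- Own three-reading SD: 4.303 × 1.155 = 4.97 SD (m = 1); 4.303 × 0.816 = 3.51 SD (m = 3). These are too large to be useful, which is why a pooled estimate is preferable.

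**Step 7: what the stricter threshold costs.** Take a true effect of two CoVs, one conditioned reading and a known CoV.
- At 1 CoV: P(Z > (1 − 2)/1.155) = 80.7%, plus 0.5% in the wrong direction, so about 81%.
- At 2.26 CoV: P(Z > (2.26 − 2)/1.155) = about 41%.

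**The case against.** **The intended meaning is probably a common scale.** Comparing percentage change with CoV%, or the kPa difference with the replicate SD, is the obvious working sense. The article cites a method source that is not at hand, and a fuller protocol or analysis plan may state the scale. This stands in part. Applying the rule with mixed units gives much higher null rates: 61–85% with the CoV as a percentage number at assumed PPT means of 150–400 kPa, and over 99% with the CoV as a fraction. Those rates describe a reading that was hardly intended and deserve no weight. The text still names two quantities that cannot be compared.

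**A flat claim that half of people with no effect would be called responders goes too far.** A reader might infer this, or attribute it to the units. The 48% arises only once the unit mismatch has been removed; it comes from the threshold. It also needs each person's own CoV and a single conditioned reading. The article fixes neither: within-participant CoV can mean a cohort-level estimate, and the PPT paragraph defines PPT as a mean of three replicates. A single reading under the cuff is the more natural reading, but the supported result is the range of 22–48%.

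**Harm to prediction, reliability or validity is not shown.** A reader might infer that misclassification dilutes these. The article separately defines a signed, continuous CPM effect. Its Data analysis section describes intraclass correlations, correlations, regression and multivariable models without saying that any uses the responder label. Nor does it say that sub-threshold values are zeroed or dropped. This objection stands.

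**The article promises no 5% error rate.** True: 5% is a convention, and a stricter cut-off misses more real effects. But the rule is offered as an allowance for measurement error, and a cut-off that ignores the error of the difference does not provide one.

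**Conclusion.** The rule is wrong as written on two counts. It compares a pressure with a dimensionless ratio. Once both are on one scale, a one-CoV cut-off still does not account for the measurement error of the difference: it is below one error SD with one conditioned reading and only 1.225 error SDs with three.

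Its size is a null rate of about 48% (own CoV) or 39% (pooled CoV) with one conditioned reading, and about 35% or 22% with three, both directions counted. These rest on independent normal errors of equal SD and, for the pooled figures, on a CoV that is well estimated and similar across people. No combination comes near a conventional 5%.

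The finding concerns the definition of the label. Any effect on the prognostic, reliability or validity results is conditional on the label being used there, which the article does not show.

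**What to change.** 1. **One scale.** Either express CPM as a percentage of the unconditioned mean PPT and compare it with CoV%, or compare the kPa difference with the within-participant SD in kPa.
2. **Conditioned readings.** State how many are taken.
3. **Threshold.** Set it from the error SD of the difference, using a within-participant estimate pooled over participants and calculated separately for the laboratory and clinical devices. For a 5% two-sided null rate this is 2.26 × pooled CoV with one conditioned reading, or 1.60 × with three. If another error rate is preferred, name it and derive the multiplier in the same way.
4. **Use.** State that the signed continuous CPM effect enters the prognostic, validity and reliability models, and that the responder label is descriptive.

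This changes wording only, with the same data, and the article reports that recruitment is still open. The price is fewer labelled responders and more missed modest effects: for a true effect of two CoVs with one conditioned reading, detection falls from about 81% to 41%. The pooled multiplier also assumes a similar CoV across the four diagnostic groups, which the unconditioned replicates allow the study to check.

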**Methods and analysis:**

This prospective observational study will recruit 250 individuals with inflammatory arthritis, osteoarthritis, chronic low back pain or fibromyalgia from existing cohorts, primary or secondary care. Participants will complete validated patient-reported outcomes at baseline, 6 and 12 weeks, with no additional intervention. The risk stratification tool completed at baseline will include clinical QST (Pressure Pain Threshold, Temporal Summation of Pain, Conditioned Pain Modulation), tender point count and the CAP questionnaire. Baseline laboratory versions of the clinical QST, plus Heat Pain Threshold, Offset Analgesia and the Central Sensitisation Inventory short form-9 questionnaire, will provide pain profiling to evaluate the predictive validity and psychometric properties of the tool. Data collection will include demographics, medical history, cognitive and neurological assessments and sleep quality via actigraphy (Actigraph wGT3X-BT). Interviews with patients and healthcare professionals will inform refinement, feasibility and acceptability of the tool.

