### Participants

Inclusion (must meet all criteria):

Aged 18 years or older.One or more of the following physician confirmed or self-reported diagnoses: fibromyalgia, osteoarthritis, chronic low back pain, inflammatory musculoskeletal conditions (eg, rheumatoid arthritis (RA), psoriatic arthritis (PsA), axial spondylarthritis).Musculoskeletal diagnosis and pain onset ≥3 months.Self-reported pain ≥3/10, where 0 is ‘no pain’ and 10 is the ‘worst pain imaginable’ for most days in the 3 months before baseline.

Exclusion (if any of the following apply):

Unable to give informed consent.Terminal or uncontrolled medical or mental health condition precluding them from completing the study protocol or pose a significant risk to themselves or staff.Unable to comprehend spoken to written English, due to not all questionnaires being translated and validated in other languages, and due to the nature of QST, individuals need to fully comprehend the testing procedure to ensure reported outcomes are valid.

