QST will be assessed on the brachioradialis muscle belly 5 cm from the lateral epicondyle^52^ of the dominant (PPT, CPM) and non-dominant arm (TSP), and the volar forearm of the dominant arm (Heat Pain Threshold (HPT), Offset-analgesia) (figure 2). Each laboratory and clinical QST protocol test will be undertaken in a standardised order (PPT, TSP, CPM, HPT, then offset analgesia). The order of laboratory and clinical QST will be randomised to minimise the potential for sequential effects to confound comparisons between the two modalities. These measures have previously been well tolerated by individuals with musculoskeletal pain and will be conducted regardless of their pain status.

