### Data analysis

Pain profiling will be undertaken irrespective of condition. Multivariate modelling (principal component analysis, cluster analysis or latent class analysis) to identify distinct pain patterns.Between-group comparisons (eg, independent T-tests, Mann-Whitney U) will explore between pain profile comparisons.Associations between pain profiles and clinical outcomes (eg, pain intensity, pain-related worrying, disability, quality of life) will be examined.Sensitivity analysis will be conducted between diagnostic groups and between matched samples.We believe that QST will identify somatosensory pain profiles, while CAP will identify psychological hypervigilance pain profiles, each associated with augmented central pain processing. Using the pain profiles combined with pain at 12 weeks, we will identify any relationship between potential augmented central pain processing and pain prognosis at 12 weeks (eg, persistent/worsening pain, pain>patient acceptable symptom state), informed by patterns of pain over 12 weeks and knowledge.Pain prognosis: Bivariable correlations will identify and permit comparison between baseline factors significantly associated with 3-month pain prognosis. Separate multivariable models will determine whether the CAP questionnaire, clinical QST or laboratory QST can increase prognostic precision beyond other clinical and demographic variables significantly associated with pain prognosis. Multivariable modelling will define whether and which combination of the CAP questionnaire and QST importantly improves prognostic determination. The proportion of the prognosis explained by each and by both the CAP questionnaire and clinical or laboratory QST will be determined.The reliability and validity of the stratification tool (combined CAP and clinical QST) will be tested across the study population, with sensitivity analysis conducted across the diagnostic groups, age, sex, social and ethnic strata.Test–retest reliability will be assessed using intraclass correlation between repeated CAP questionnaires and between two raters for simplified clinical QST.RMT, Cronbach’s alpha and confirmatory factor analysis will evaluate internal validity, consistency and factor structure. If multiple constructs with significant residual values exist, this will be further explored using principal component analysis of residuals, the eigenvalue criterion, residual correlations and theoretical understanding.Correlation analysis will assess external validity against self-reported questionnaires and laboratory QST.Mechanistic underpinning: The dataset will be randomly divided into development and validation sets. Exploratory and confirmatory factor analyses will determine whether there are subgroups of the population for whom the stratification tools function differently. Correlations between CAP scores and clinical and laboratory QST indices of augmented central pain processing will be identified. Bivariate and multivariable models will ascertain whether associations may be explained by one or more characteristics linked to maladaptive pain processing (sleep disturbance, fatigue, anxiety, depression, cognitive impact, catastrophising).Relevance to patient-centred outcomes: Bivariate associations between CAP or QST and patient-reported outcome measures scores will be determined through linear regression. The proportion of participant-reported pain or other patient-reported outcome measures explained by CAP scores, clinical and/or laboratory QST measures, will be identified as R^2^ in multivariable regression.Qualitative data will be analysed using reflexive thematic analysis following the stages outlined by Braun and Clarke.^97^ A reflexive journal will be kept throughout the data collection process. Data will be coded inductively primarily, while also being informed by the Normalisation Process Theory^90 91^ commonly used to support evaluation in health interventions and inform the tool’s theoretical acceptability and feasibility. A ‘critical friend’^98^ will code a sample of transcripts independently until consensus is reached. After the consensus is reached, all remaining transcripts will be coded. NVivo V.15 will assist in managing, analysing, and visualising the qualitative data set. A thematic map may also visually represent the main themes developed.

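### Baseline analgesic use is recorded by class, but no stated model names it, and it can reach the prognostic models only through a significance screen, so QST associations may be confounded in either direction

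*Protocol article*

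**What the plan says.** All references are to the protocol article.

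- **Eligibility (Participants).** The exclusions concern consent, English comprehension and a "Terminal or uncontrolled medical or mental health condition precluding them from completing the study protocol" or posing a risk. None concerns analgesics.
- **Testing (Experimental procedures).** The tests "will be conducted regardless of their pain status". No condition on medication before testing is stated.
- **Follow-up (Abstract, Methods and analysis).** Participants are followed "with no additional intervention", so usual care continues.
- **Data collected (Experimental procedures).** "Potential confounders will also be included in the questionnaire, including demographics" and comorbidities. The next sentence reads "Regular and current medication used will be classified as analgesic", with subclasses that include opioids and anti-neuropathic drugs. On timing: "Questionnaires completed at baseline, 6, and 12 weeks will assess clinical characteristics associated with maladaptive pain processing, patient-centred outcomes and potential confounders".
- **Prognostic models (Data analysis, pain prognosis).** Baseline factors are screened by bivariable correlation. The models then ask whether CAP or QST "can increase prognostic precision beyond other clinical and demographic variables significantly associated with pain prognosis".
- **Mechanistic models (Data analysis, mechanistic underpinning).** These ask whether associations are explained by characteristics linked to pain processing: "sleep disturbance, fatigue, anxiety, depression, cognitive impact, catastrophising".
- **Sensitivity analyses (Data analysis).** Reliability and validity are examined across diagnosis, age, sex, social and ethnic strata. Pain profiles are compared between diagnostic groups and matched samples; the matching variables are not given.

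**The concern.** Opioids and anti-neuropathic drugs are prescribed because of pain, and they can also change the response to a test stimulus. Such a variable can confound the link between QST and pain, and the link between QST and CAP.

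Its own association with 12-week pain mixes two opposing influences. People in more pain are more likely to be treated, and treatment may lower their pain. The net association can be small enough to fail a significance test while the drug still shifts the QST values. The stated selection rule would then drop the variable where it is needed.

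The attribution to central mechanisms and the comparison of QST with CAP are at stake, more than prediction itself. The Introduction lists detecting treatment response before symptoms improve among the tool's goals, so the authors themselves expect treatment to be able to move the tool.

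**Working it through.** There is no figure in the plan to reproduce on this point. The check is mainly of the text, with one illustration.

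**Step 1: can baseline medication enter a stated model?**

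| Analysis | Stated rule | Route for analgesic class |
|---|---|---|
| Prognostic models | clinical and demographic variables that are significant for prognosis | possible, only by passing the screen |
| Mechanistic models | six named characteristics | none stated |
| Reliability and validity strata | diagnosis, age, sex, social, ethnic | none stated |
| Pain-profile sensitivity analysis | diagnosis, matched samples | unknown |

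So no model names medication, but the prognostic wording can admit it.

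**Step 2: how large could confounding be?** The documents give no correlation of medication with QST or pain, so these are assumed. Let r be the unadjusted correlation of a predictor with 12-week pain, a the correlation of medication with the predictor, and b that of medication with pain. The adjusted correlation is

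(r − ab) / √[(1 − a²)(1 − b²)].

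Take r = 0.15, the planning value in Sample size, and a and b each between 0.1 and 0.3 in absolute value.

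- Same sign, 0.1 and 0.1: (0.15 − 0.01)/0.99 = 0.141.
- Same sign, 0.3 and 0.3: (0.15 − 0.09)/0.91 = 0.066.
- Opposite sign, 0.1 and 0.1: (0.15 + 0.01)/0.99 = 0.162.
- Opposite sign, 0.3 and 0.3: (0.15 + 0.09)/0.91 = 0.264.

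Score the predictor so that higher means more sensitive. If treated people are the more sensitive ones and have more pain, the unadjusted figure is inflated. If drugs dampen the test in people with more pain, it is masked. Both are plausible.

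**Step 3: would the screen catch it?** Assume a two-sided 5% screen (the level is not stated) and the 200 completers anticipated in Sample size. By Fisher's z, an observed correlation must exceed tanh(1.96/√197) = tanh(0.1396) = 0.139 to be significant. A medication class with b = 0.1 falls below this. With a = 0.3 and b = 0.1 the adjusted correlation is still 0.12/√(0.91 × 0.99) = 0.126 (same sign) or 0.18/√(0.91 × 0.99) = 0.190 (opposite sign), against 0.15 unadjusted. A screened-out drug class can therefore move the estimate.

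**Step 4: would restricting to unchanged treatment help the accuracy figures?** Suppose 100 people with persistent pain and 100 without, with sensitivity and specificity of 75% if nobody changed treatment: TP 75, FN 25, FP 25, TN 75. Assume treatment is started in 30% of tool-positives and 10% of tool-negatives, and succeeds in half.

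- Everyone, under usual care: TP 63.75, FP 36.25, FN 23.75, TN 76.25. Sensitivity is 63.75/87.5 = 73%; specificity is 76.25/112.5 = 68%.
- Only those without a change: TP 52.5, FP 17.5, FN 22.5, TN 67.5. Sensitivity is 52.5/75 = 70%; specificity is 67.5/85 = 79%.

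Restriction moves sensitivity further from 75% and overshoots on specificity. It selects on a post-baseline event related to the tool result.

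**The case against.** The strongest reply is that this is a condensed article. Data analysis gives no full adjustment set: neuropathy is expressly called a potential confounder and comorbidities are listed as confounders, yet neither is named there. The full protocol or analysis plan may name medication. That stands, and silence alone would not be a finding. What remains is the rule the article does state: selection by significance against prognosis. That rule is weak for this variable whatever the final list contains.

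A reader might infer that the models exclude medication altogether. The text does not support this. Baseline analgesic class is a clinical variable that the prognostic wording can admit, and the objectives also refer to clinical variables. The six mechanistic characteristics are offered as candidate explanations, not as a complete list of confounders.

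A reader might also infer that QST associations are biased toward zero, to CAP's advantage. The documents give no drug prevalence, drug effect or correlation, and Step 2 shows that either direction is possible.

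Finally, a reader might hold that a flagged participant who is treated and improves is wrongly counted as a false positive. The study predicts pain under usual care, and for that target the participant is a genuine false positive. The article does not say that tool results are given to treating clinicians, so a treatment difference by tool result is itself an assumption.

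**Conclusion.** The concern holds in limited form. As the article describes them, the analyses leave baseline analgesic use to a significance screen in the prognostic models and name it nowhere in the mechanistic ones. QST–CAP and QST–pain associations, and their reading as evidence of central pain processing, may therefore be confounded.

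Size and direction are unknown. The range 0.066 to 0.264 around 0.15 rests wholly on assumed medication correlations and shows only that the effect need not be trivial.

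The planned sensitivity and specificity are not in error on this account. For prediction under usual care, leaving treatment unadjusted is legitimate. This is a worthwhile correction to analysis wording and does not invalidate the design.

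**What to change.** In Data analysis:

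1. Enter baseline opioid use (yes/no) and anti-neuropathic use (yes/no), without a significance screen, in the multivariable prognostic and mechanistic models that contain a QST measure. Report the QST–CAP and QST–pain associations with and without these terms. Both versions are needed because drug use also partly marks pain severity.
2. If medication is recorded at 6 and 12 weeks, tabulate analgesic changes by tool risk level, as description only. The questionnaire timing suggests repeat recording, but the medication sentence gives no time point, so this should be confirmed.
3. Keep the usual-care sensitivity and specificity as the estimate. Do not recompute them in participants without a treatment change, for the reason in Step 4.

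The cost is two extra model terms against about 200 completers, plus a table. Baseline subclasses are already collected. No change to eligibility, testing or treatment is proposed. Recruitment is still under way according to Study design and setting, so the wording can be fixed before the analysis.
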